### Intervention description {11a}

We are evaluating a supply-demand intervention in a clinic-randomized design. The trial methods are provided here.

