### Sample size {14}

Table 4 shows the expected number of participants included in each study activity. We assume that the proposed sample sizes shown below for in-depth interviews will allow us to reach saturation. Based on facility volume and preliminary findings, we conservatively expect to deliver PPFP promotions to 12,714 in the 12 intervention facilities (18% of reproductive age women in the catchment area) and 21,383 women/couples total across the 17 facilities (12 intervention plus 5 training facilities).

**Table 4 Tab4:** Expected number of participants included for each study activity

Specific aim	Activity	Total participants
Aim 1	In-depth interviews	12 facility directors 24 nurses in-charge of L&D and family planning 24 CHWs 5 MOH stakeholders
Aim 2	Intervention trainings	98 government facility PPFP promoters 68 community health worker promoters 78 government facility PPFP providers (70 certified) 36 Happy Client promoters
	Intervention recipients	We expect to deliver PPFP promotions to *n* = 12,714 women/couples
	In-depth interviews	25 women/couples 25 providers 25 stakeholders

We assume based on our pilot that promotions will reach 75% of pregnant women in health centers. Also extrapolating from our pilot data, we also expect to insert 3687 PPIUDs and 1399 PP implants in the 12 intervention facilities (6201 PPIUDs and 2352 PP implants total across the 17 facilities) (Table 5). Given the facility volume and previous experience, PPFP service delivery to this number of women is highly feasible. Sample size and power calculations account for intra-cluster correlation (ICC) which considers the between-cluster correlation, within-cluster correlation, and repeated measures. We assume pooled between- and within-cluster ICCs and a homogeneous intervention effect over time. We have > 80% power to detect all differences in the expected proportions shown in Table 5 comparing PPFP intervention to control.

**Table 5 Tab5:** Expected deliverables during the study time period, *n* = 12 intervention facilities. Power to detect the differences between standard of care control and intervention: > 80%

Stakeholders	Control^**a**^			PPFP intervention		
	***N*** events	Denominator	Expected %	***N*** events	Denominator	Expected %^**b**^
Clinic directors engaged	2	12	17%	12	12	100%

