**Clients delivering at implementation facilities**						
Promotions to pregnant or postpartum women/couples	268	17,870	2%	12,714	17,870	71%
PPIUD insertions	20	268	7%	3687	12,714	29%
PP implant insertions	14	268	5%	1399	12,714	10%

^a^Data from *n* = 12 government clinic logbooks, 2018

^b^Estimated from the pilot study [5]

^c^In ANC, L&D, FP, and IV

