#### Effectiveness

##### Primary analyses

We will tabulate, by facility, a total number of all PPFP methods provided and the proportion of PPFP uptake among women who delivered at one of our facilities (overall and by method type). PP LARC uptake (by method type) will be evaluated using logistic regression and general estimating equation methods to account for the clinic-randomized design. The main predictor will be the intervention versus the control arm. For example, the following generalized linear mixed model will compute the adjusted odds ratio for taking up a PP implant: *Y*_*ijl*_ = *β*0 + *β*1 × (intervention_*ij*_) + *β*2 × (covariates_*ij*_) + *β*3 × (intervention_*ij*_ × covariates_*ij*_) + *β4*_*j*_ + *u*_*i*_ + *ε*, where *i* = clusters*, j* = time periods, *l* = individuals, *β*1 = fixed effect for intervention, *β*2 = fixed effects for covariates, *β*3 = fixed effects for interactions, *β*4_*j*_ = fixed effect for time, *u*_*i*_ = random effect for ICC, and *ε*_*ijl*_ = random residual. Covariates assessed as potential confounders will include facility volume, service volume-to-staffing ratio, and number of promotions received. Outcomes will be reported as adjusted odds ratios with 95% confidence intervals. We hypothesize that the intervention will significantly increase PP LARC uptake by comparing intervention versus control. We will also assess the independent effect of each promotional strategy on PP LARC uptake. Every promotion will be recorded and we will estimate the independent effect of receiving CHW counseling, video-based promotions, or Happy Client promotions (treating each strategy as an independent, dichotomous exposure of interest) on PPFP uptake using adjusted multivariate regression modeling with general estimating equations methods.

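### The primary uptake model lists the number of promotions received, a consequence of the intervention, among its candidate confounders

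*Protocol article*

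**What the plan says.** The relevant text is in the protocol article, Statistical methods {20a}, Effectiveness, Primary analyses.

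- The contrast of interest is allocation: "The main predictor will be the intervention versus the control arm".
- The candidate covariates are then named: "Covariates assessed as potential confounders will include facility volume, service volume-to-staffing ratio, and number of promotions received".
- One example equation is given, a mixed model for implant uptake. It has an intervention term (β1, labelled "fixed effect for intervention"), covariates (β2), intervention × covariate products (β3, labelled "fixed effects for interactions"), a period effect and a clinic random effect.
- On reporting: "Outcomes will be reported as adjusted odds ratios with 95% confidence intervals".

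No primary model without promotions is given.

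Elsewhere the article treats promotions as something the intervention produces:

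- Intervention description {11a}: "We are evaluating a supply-demand intervention in a clinic-randomized design". The section on demand creation training describes promotion as the demand side.
- Table 4 counts intervention recipients by promotions: "We expect to deliver PPFP promotions to" 12,714 women or couples.
- Table 1 lists clients receiving PPFP information as a Reach outcome. The Reach and adoption paragraph of {20a} hypothesises that the intervention will increase it.
- Table 5, row "Promotions to pregnant or postpartum women/couples", expects 268 of 17,870 (2%) under control and 12,714 of 17,870 (71%) under the intervention.

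**The concern.** A confounder of a randomised comparison has to be associated with allocation without being caused by it. The number of promotions a woman receives follows from whether her clinic has crossed over, and the article hypothesises exactly that. It also lies on the path by which the programme is meant to raise uptake.

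Conditioning on such a variable removes the part of the effect that it transmits. What is left is approximately the effect of the remaining components, such as provider training and certification, at a fixed level of promotion. That is not the total effect of intervention versus standard of care, which is the superiority question. At the extreme, a programme that works almost entirely by creating demand could be reported as having little or no effect.

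The interaction terms raise a second problem. Once they are in the model, β1 no longer has a fixed meaning as the intervention effect. It depends on where zero lies on each covariate's scale.

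**Working it through.** **1. Table 5's own figures.** Promotions: 268/17,870 = 1.5% (printed 2%) and 12,714/17,870 = 71.1% (printed 71%). PPIUD: 20/268 = 7.5% (printed 7%) and 3687/12,714 = 29.0% (printed 29%). Implant: 14/268 = 5.2% (printed 5%) and 1399/12,714 = 11.0% (printed 10%).

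**2. Would a confounder screen keep promotions?** The odds ratio linking allocation to promotion is (12,714/5,156) / (268/17,602) ≈ 162. Promotion is also expected to drive uptake. Almost any screen based on association, or on change in the estimate, would retain it.

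**3. Illustration of scale.** Assume that every insertion in Table 5 is in a promoted woman. The insertion denominators suggest this but the article does not state it.

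| Method | OR, all 17,870 delivering women per arm | OR, promoted women only |
|---|---|---|
| PPIUD | (3687/14,183) / (20/17,850) ≈ 232 | (3687/9,027) / (20/248) ≈ 5.06 |
| Implant | (1399/16,471) / (14/17,856) ≈ 108 | (1399/11,315) / (14/254) ≈ 2.24 |

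The gap is not an artefact of the odds ratio changing under conditioning. As risk ratios, the same counts give 3687/20 ≈ 184 against 29.0%/7.46% ≈ 3.9 for PPIUD, and 1399/14 ≈ 100 against 11.0%/5.22% ≈ 2.1 for implants. In both cases the factor lost is the rise in promotions, 12,714/268 ≈ 47.

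**4. Direction under an actual stepped-wedge fit.** This simulation rests on assumed inputs: 12 clinics, 4 steps, 5 periods, 150 women per clinic-period, and promotion reach of 1.5% versus 71%. Logistic models included clinic and period effects.

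| Assumed log OR: supply / per promotion | OR without promotions | OR adjusted for promotions | OR with promotions and interaction |
|---|---|---|---|
| 0 / 1.5 | 9.15 | 0.97 | 0.99 |
| 0.5 / 1.2 | 10.26 | 1.77 | 1.76 |
| 1.0 / 0.8 | 8.2 | 2.57 | 2.68 |

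When the whole effect passes through promotions, adjustment removes it. When some passes through supply, roughly that part remains.

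**5. The interaction terms.** For a covariate Z, the intervention log odds ratio at Z = z is β1 + β3·z, so β1 is the effect at z = 0. For facility volume and the volume-to-staffing ratio, zero lies outside the data, because the facilities were chosen as high-volume. The article does not say whether covariates are centred.

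**The case against.** Several points on the other side have force.

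- **Inclusion is conditional.** Covariates are to be assessed as potential confounders, and the equation is offered as an example. A reader might infer that adjustment for promotions is already fixed. The text does not say so; it makes retention very likely.
- **Promotions are a component.** A reader might conclude that the model adjusts for the intervention itself. That is too strong: training, certification and provider reimbursement are also part of it. Adjustment leaves a partial effect, not necessarily none.
- **The Table 5 odds ratios are a construction.** Table 5 does not give insertions over all deliveries, and 232 and 108 require that no unpromoted woman had an insertion. The plan names a count of promotions and indexes covariates by clinic and period, so restricting to promoted women is a different adjustment. The share of effect lost in that illustration should not be read as a forecast. A clinic-period mean would still arise after allocation and would be nearly collinear with intervention status.
- **The interaction point is narrower than it may look.** Zero promotions is well inside the data: by Table 5 about 98% of control women and 29% of intervention women receive none. Adjusted odds ratios can be evaluated at covariate means, and centring is a detail an analysis plan may settle. Any figure for lost precision would need a between-facility spread in volume, which the article does not give.

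None of this makes a post-allocation mediator a legitimate candidate confounder in the primary model.

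**Conclusion.** Wrong as written, in a limited and easily corrected way. The only primary model described admits as a potential confounder a variable that the same article treats as an effect of the intervention. If it is retained, the headline odds ratio would be pulled away from the total effect and could be close to 1 if the programme works mainly through promotion.

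The conclusion rests on the article's account of promotions and on the expected contrast of 2% versus 71%. The direction also assumes, as the trial does, that promotions raise uptake. The size cannot be derived from the document. The odds ratios of 232 versus 5.1 and 108 versus 2.2, and the simulated values, show scale and direction only.

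Facility volume and volume-to-staffing ratio are unobjectionable as main effects if measured before crossover. The interaction terms call for clarification: unless covariates are centred, β1 should not be described or reported as the intervention effect.

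**What to change.** - Delete the number of promotions received from the primary model's covariates. Adjust only for facility-level variables measured before crossover: baseline volume and baseline volume-to-staffing ratio.
- Report the intervention effect from a primary model without intervention × covariate terms. Put any interactions in a secondary effect-modification analysis with centred covariates.
- Keep promotion number and type in the separate analyses already planned: the strategy comparisons at the end of the Primary analyses paragraph, and the trend test on counselling sessions under Descriptive analyses {20b}. Label these as non-randomised.
- Do not add age or parity unless they are recorded for all delivering women. Under {18a} they come from government Family Planning logbooks, which may omit women who took no method. With the complete-case primary analysis in {20c}, adjusting for them could select on the outcome.

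The cost is wording in the protocol and analysis plan. No new data or change in conduct is needed.

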**Methods:**

In a type 2 effectiveness-implementation hybrid study, we will evaluate the impact of our PPFP intervention on postpartum LARC (PPLARC) uptake in a clinic-randomized trial in 12 high-volume health facilities in Kigali, Rwanda. We will evaluate this hybrid study using the RE-AIM framework. The independent effectiveness of each PPFP demand creation strategy on PPLARC uptake among antenatal clinic attendees who later deliver in a study facility will be estimated. To assess sustainability, we will assess the intervention adoption, implementation, and maintenance. Finally, we will evaluate intervention cost-effectiveness and develop a national costed implementation plan.

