## Statistical methods

### Statistical methods for primary and secondary outcomes {20a}

#### Reach and adoption

We will tabulate, overall and by facility, the number of stakeholders engaged, providers trained, promoters trained, providers certified and pre/post-training evaluation scores, and clients who received one-on-one counseling. We hypothesize increases comparing intervention versus standard of care in stakeholders engaged, providers trained to promote and provide PPFP, and couples/clients receiving information about PPFP (Table 5). We expect 90% of trainees will receive certification to promote and provide PPFP.

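### The primary model lists the number of promotions received as a potential confounder, although promotions are part of the intervention; keeping it would remove the effect that runs through them

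*Protocol article*

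**What the plan says.** The abstract sets the target as the effect of the whole package: "we will evaluate the impact of our PPFP intervention on postpartum LARC (PPLARC) uptake". The Primary analyses paragraph under Effectiveness follows this: "The main predictor will be the intervention versus the control arm". The example model there has a fixed effect for intervention (β1), fixed effects for covariates (β2), intervention-by-covariate products (β3, described as "fixed effects for interactions"), period effects and a cluster random effect.

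On the covariates it says: "Covariates assessed as potential confounders will include facility volume, service volume-to-staffing ratio, and number of promotions received". On reporting: "Outcomes will be reported as adjusted odds ratios with 95% confidence intervals".

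Elsewhere the protocol treats promotions as something the intervention produces. The demand creation training section describes them as a component. Table 1 lists them as a Reach measure. The Reach and adoption analysis hypothesises that the intervention raises the number of "couples/clients receiving information about PPFP". The article gives no total-effect model without promotions as the main estimate, and no mediation analysis.

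**The concern.** A confounder is a common cause of exposure and outcome. Here the exposure is the clinic's randomised crossover, which cannot be caused by promotions delivered later. The direction is the reverse: crossover produces promotions, and promotions are meant to produce uptake. Conditioning on them blocks that path, and β1 then describes what remains, broadly the supply side (trained and certified inserters).

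The interaction terms sharpen the problem. If the product of intervention and promotions enters the model, β1 becomes the intervention effect in women with zero promotions, which is not the question the trial asks.

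The headline odds ratio is at stake. It would be presented as the effect of the intervention against standard of care but would understate it, by an amount that depends on how the covariate is coded.

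**Working it through.** **Inputs, all from Table 5 (12 intervention facilities).**
- "Promotions to pregnant or postpartum women/couples": 268/17,870 = 1.5% under control (printed 2%); 12,714/17,870 = 71% under intervention.
- "PPIUD insertions": 20/268 = 7.5% (printed 7%); 3,687/12,714 = 29.0%.
- Implant insertions: 14/268 = 5.2%; 1,399/12,714 = 11.0% (printed 10%).

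The printed percentages thus reproduce to within rounding or one point. Uptake among women who received no promotion is not given, so it is an assumption below.

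**Step 1: no uptake in unpromoted women.** The total odds ratio uses all 17,870 deliveries in each condition. The conditional odds ratio holds promotion fixed as yes/no. Share lost = 1 − ln(conditional OR)/ln(total OR).
- PPIUD total: (3,687/14,183)/(20/17,850) = 232. Conditional: (3,687/9,027)/(20/248) = 5.06. Share lost: 1 − 1.622/5.447 = 70%.
- Implant total: (1,399/16,471)/(14/17,856) = 108. Conditional: (1,399/11,315)/(14/254) = 2.24. Share lost: 1 − 0.808/4.685 = 83%.

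**Step 2: some uptake in unpromoted women.** Let b be that uptake, assumed equal in both conditions. Each condition's overall risk is coverage × risk if promoted + (1 − coverage) × b. For PPIUD at b = 1%, control is 0.015 × 7.46% + 0.985 × 1% = 1.10%, intervention is 0.711 × 29.0% + 0.289 × 1% = 20.9%, and the total OR is 23.9. Two conditional estimates are compared with the total: the OR among promoted women only, and the intervention OR from a logistic model with intervention and promotion (yes/no) fitted to both strata, without interaction, clustering or period terms.

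| Method | b | Total OR | OR, promoted only | Share lost | OR, pooled model | Share lost |
|---|---|---|---|---|---|---|
| PPIUD | 0.5% | 43.1 | 5.06 | 57% | 2.31 | 78% |
| PPIUD | 1% | 23.9 | 5.06 | 49% | 1.85 | 81% |
| PPIUD | 2% | 12.7 | 5.06 | 36% | 1.52 | 84% |
| Implant | 0.5% | 15.1 | 2.24 | 70% | 1.41 | 87% |
| Implant | 1% | 8.2 | 2.24 | 62% | 1.26 | 89% |
| Implant | 2% | 4.4 | 2.24 | 45% | 1.16 | 90% |

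The pooled model loses more because its unpromoted stratum has an odds ratio of 1 by assumption.

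**Step 3: promotions as a number, which is what the protocol lists.** A stepped-wedge simulation with GEE logistic models assumed 12 clinics, 5 periods, 300 women per clinic-period, Table 5 coverage and uptake, and b of 0.5% or 2%, equal in both conditions. Share of the log odds ratio lost, relative to the model without promotions:
- linear count: about 21–35%;
- categorical count: about 76–88% when part of the effect came through supply, and essentially all of it when the whole effect ran through promotions;
- linear count with its intervention product: β1 lost about 11–30%;
- any promotion (yes/no) with its intervention product: β1 lost about 98–100%, as must happen when unpromoted women are assumed to gain nothing.

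**The case against.** The strongest reply is that the protocol says only that these covariates will be assessed as potential confounders. It states no selection rule, and final selection is commonly left to the analysis plan. A reader might infer that any confounder assessment is bound to keep the variable. The text does not support that, because no change-in-estimate or other criterion is given. Inclusion is possible, not fixed. But promotions should not be a candidate at all, so the sentence is wrong whatever the rule.

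Second, a reader might infer that the adjusted odds ratio would certainly lose most of the effect, or that the trial would report none. That does not stand as a certainty. The loss depends on uptake in unpromoted women and on coding, neither of which is stated. The intervention also has a supply side: before the trial no providers at these facilities are trained to insert postpartum IUDs, and Table 5 leaves odds ratios of about 5 and 2.2 among promoted women. Those are the contrasts Table 5 itself prints; the totals of 232 and 108 are built here from all deliveries. If trained inserters also raise uptake in unpromoted women, the pooled losses shrink.

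Third, the example model indexes covariates by clinic and period, so a reader might infer severe collinearity with the intervention indicator. The article does not support a figure for this. The stepped-wedge schedule is not shown, no spread of coverage is given, and the variable reads naturally as woman-level, since clients are tracked individually and each promotion is recorded.

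**Conclusion.** The point holds in a limited form. The protocol offers a post-randomisation mediator as a potential confounder of its primary randomised comparison, and nothing else in the article corrects this. If the variable is used, β1 does not estimate the total effect, whatever the coding.

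The amount removed is uncertain. With promotion as yes/no it is 70% (PPIUD) and 83% (implant) of the log odds ratio if unpromoted women have no uptake. At 0.5–2% unpromoted uptake, equal in both conditions, a model pooling promoted and unpromoted women loses 78–84% and 87–90%. The odds ratio among promoted women alone implies 36–57% and 45–70%. A linear count removed about 21–35% in simulation. The supported statement is that the part running through promotions is removed, possibly most of it.

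**What to change.** In the Primary analyses paragraph, and in the analysis plan if it repeats the list, delete the number of promotions received from the covariates of the intervention-versus-control model, together with any interaction involving it. Limit adjustment to facility values fixed before the clinic crosses over; the organizational readiness checklist already collects facility volume and staffing. Use promotions only in the separate promotional-strategy analysis that the same paragraph describes, or in a mediation or dose-response analysis labelled as secondary.

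The cost is one sentence. It needs no new data, and no planned analysis of promotions is lost.

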### Objectives {7}

Aim 1: Implement the intervention in 12 high-volume health facilities: Guided by the Consolidated Framework for Implementation Research [9, 10], we will engage stakeholders and assess facility organizational readiness prior to implementation. No PPFP activities are currently taking place in these facilities. We will implement the PPFP intervention in a clinic-randomized stepped-wedge design. We expect to deliver PPFP promotional counseling to over 21,000 pregnant or postpartum women/couples.

Aim 2: Evaluate intervention effectiveness and implementation: The RE-AIM framework [11] will guide the outcome evaluation. We hypothesize that the intervention will significantly increase the number of stakeholders engaged, PPFP providers and promoters, couples/clients receiving information about PPFP, and LARC uptake comparing intervention versus standard of care. We expect PPFP client satisfaction will be high, and side effects will be rare. The independent effectiveness of each demand creation strategy on LARC uptake will be estimated. We assess the measures of intervention adoption, implementation, and maintenance at the patient, provider, and stakeholder levels to assess the intervention sustainability.

Aim 3: Evaluate intervention cost-effectiveness and cost-utility: We employ standard methods [12, 13] to estimate the costs and incremental cost-effectiveness and cost-utility of the intervention relative to the standard of care from the societal perspective. The cost-effectiveness of each demand creation strategy will be estimated. We hypothesize that the intervention will be cost-saving relative to the standard of care. A costed implementation plan will be developed to guide Rwandan MOH decision-making for the nationwide roll-out of PPFP services.

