### Eligibility criteria {10}

Aim 1: Provider and stakeholder in-depth interviews

All participants will be government employees of at least 18 years of age who provide written informed consent to participate in in-depth interviews.

Aim 2: Implement PPFP services in a cluster-randomized stepped-wedge trial

Eligible PPFP providers will be women working in L&D or family planning at one of the study facilities. Eligible Happy Client promotors will be postpartum women who received promotions and selected a PPFP method. Eligible nurse and CHW promotors will be women working as nurses or CHWs at one of the intervention facilities. All women eligible for PPFP services in this study will be at any stage of pregnancy or up to 14 weeks postpartum and receiving ANC, L&D, IV, or postpartum services at one of the intervention facilities.

Aim 3: Client/couple, provider, and stakeholder in-depth interviews

All participants will be at least 18 years of age who provide written informed consent to participate in the in-depth interviews. Clients/couples will be those who received PPFP counseling. Providers and stakeholders will be government employees.

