#### PPFP demand creation training

We will train the government clinic staff in family planning, ANC, L&D, and IV to promote PPFP at the selected facilities. Trainings will comprise a 3-h-long didactic session led by the trained research staff followed by two supervised counseling sessions. CHWs from the health centers in charge of pregnant women and newborn health will receive a 1-day training on the PPFP flipchart. If interested in PPFP, women will be referred to the facility by their CHW. We will develop training materials to coach Happy Clients to discuss their own experiences with PPFP and address common concerns (as identified in our formative work and also addressed in the promotional flipchart). Happy Clients will be distributed equally across intervention facilities, affiliated with only one facility, and will be partnered with trained PPFP counselors. Finally, we will create an educational video in which a nurse counselor describes the PPFP flipchart information, visually shows each PPFP option, and men and Happy Clients give brief testimonies as to their experiences with different PPFP methods. Videos providing PPFP information will be shown in the ANC, L&D, and IV waiting areas in intervention facilities.

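### The Happy Client yes/no contrast leaves out one-on-one counseling, so it cannot separate the Happy Client from the counselor she works with

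*Protocol article*

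**What the plan says.** The Objectives commit to strategy-level estimates: "The independent effectiveness of each demand creation strategy on LARC uptake will be estimated". The Primary analyses section says how: "we will estimate the independent effect of receiving CHW counseling, video-based promotions, or Happy Client promotions", with the coding "treating each strategy as an independent, dichotomous exposure of interest", "on PPFP uptake using adjusted multivariate regression modeling with general estimating equations methods". Three strategies are listed. One-on-one counseling by clinic staff, which the PPFP logbook records, is not one of them. No reference group or adjustment set is given for this model. For the arm comparison, the same section says: "Covariates assessed as potential confounders will include facility volume, service volume-to-staffing ratio, and number of promotions received".

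Two other places bear on the contrast. Under PPFP demand creation training, Happy Clients are "affiliated with only one facility, and will be partnered with trained PPFP counselors". The abstract's Methods paragraph sets the population for the strategy estimates: "on PPLARC uptake among antenatal clinic attendees who later deliver in a study facility will be estimated". That population is not limited to women who were counseled.

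**The concern.** If a Happy Client usually works beside a trained counselor, women exposed to her have usually been counseled as well. Women not exposed to her are a mixture of counseled women and women who received no promotion. A yes/no Happy Client term then picks up part of the counseling effect. Coding the strategies as independent assumes away a link that the training section sets up.

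Time can add to this. The eligibility section says: "Eligible Happy Client promotors will be postpartum women who received promotions and selected a PPFP method". Exposure may therefore be less common soon after a clinic crosses over. That is also when supervision is daily before it moves to on-call, and when the month-2 fidelity check and any re-training take place. Calendar period alone does not capture time since crossover when clinics cross over at different dates.

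The arm comparison is not affected. At stake is the answer to a question posed in the Background, whether the Happy Client model increases effectiveness. The Objectives also plan a cost-effectiveness estimate for each strategy and a costed plan for national roll-out, both of which would draw on strategy-level results.

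**Working it through.** **Inputs from Table 5 (intervention columns), reproduced first**

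- Promotion coverage: 12,714/17,870 = 71.1% (stated 71%). Not promoted: 5,156/17,870 = 28.9%.
- PPIUD: 3,687/12,714 = 29.0% (stated 29%).
- Implant: 1,399/12,714 = 11.0%. The table prints 10%; I use the counts.
- Any LARC among promoted women: (3,687 + 1,399)/12,714 = 5,086/12,714 = 40.0%, counting one insertion per woman.
- Control column, any LARC: (20 + 14)/268 = 12.7%.

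**Assumptions (not in the article)**

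- Promoted women are taken as counseled women, and every Happy Client contact is with a counseled woman.
- The Happy Client adds nothing to counseling.
- h, the share of all women who meet a Happy Client, runs from 1% to 30%. The article gives 36 Happy Clients but not their reach.
- u, uptake in uncounseled women, runs from 0 to 20%.

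**Crude odds ratio for an ineffective Happy Client**

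With c = 0.711 and p = 0.400, exposed uptake is p. Unexposed uptake is q = [p(c − h) + u(1 − c)]/(1 − h). The odds ratio is [p/(1 − p)]/[q/(1 − q)].

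- Low end, h = 0.01 and u = 0.20: q = (0.400 × 0.701 + 0.20 × 0.289)/0.99 = 0.342, so OR = 0.667/0.519 = 1.28.
- High end, h = 0.30 and u = 0: q = (0.400 × 0.411)/0.70 = 0.235, so OR = 0.667/0.307 = 2.17.

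| u | h = 1% | h = 10% | h = 20% | h = 30% |
|---|---|---|---|---|
| 0 | 1.69 | 1.79 | 1.94 | 2.17 |
| 12.7% | 1.41 | 1.47 | 1.54 | 1.65 |
| 20% | 1.28 | 1.32 | 1.37 | 1.43 |

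For h of 1% to 30%, with u from 0 to the control figure for each method (20/268 = 7.5% and 14/268 = 5.2%), the range is 1.39 to 1.99 for PPIUD and 1.20 to 1.79 for implant.

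**Does adjustment remove it?**

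Logistic models were fitted to simulated data: 400,000 women, no clustering and no Happy Client effect. Happy Client reach was 10%, 30% or 50% of counseled women (7% to 36% of all women), with u = 0.2% or 12.7%. CHW and video exposure were either unrelated to counseling or confined to counseled women.

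| Model | Happy Client OR (true value 1) |
|---|---|
| Crude | 1.45 to 2.34 |
| CHW and video also in the model | 1.28 to 2.34 |
| Promotion count in the model | 0.58 to 1.88, depending on how promotions are counted and coded |
| Counseling term, or counseled women only | 0.98 to 1.04 |

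The promotion count is unreliable because it can contain the Happy Client contact itself. Counted that way and entered linearly, it gave 0.58 to 1.04. Counting a joint session once, also linear, gave 1.14 to 1.88.

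**The case against.** The strongest reply is that the article gives neither a reference group nor an adjustment set for this model, calls it adjusted, and is a condensed account. Those details may sit in an analysis plan that is not shown, and their absence is not an error. That stands. What the article does fix is the list of exposures and their coding as independent. Counseling is missing from that list although the article itself pairs Happy Clients with counselors. Adjustment for CHW and video, the other two listed strategies, does not repair this.

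A second reply is that every promotion is recorded and the promotion count is a named candidate confounder, so women with no promotion would be distinguished. This stands in part. With some codings the bias vanishes, with others it reverses, and the article does not say how promotions are counted or whether the count enters the strategy model.

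Third, being partnered with counselors does not establish that every Happy Client contact includes a counseling session. This is correct. The less the two overlap, the smaller the bias.

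Fourth, restricting to counseled women removes any effect a Happy Client has by drawing women into counseling, which is a plausible role for a demand creation strategy. This is a real cost of the restricted contrast and should be stated with it.

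**Conclusion.** As described, the Happy Client estimate is not an independent effect, because the contrast does not separate the Happy Client from the counselor. The size is a crude odds ratio of about 1.3 to 2.2 for any LARC when the true added effect is nil. It rests on Table 5 coverage and uptake, on promoted women being counseled, and on the assumed values of h and u. Higher reach would enlarge it.

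Four stronger readings go beyond the documents:

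- **An ineffective Happy Client would show an odds ratio near 2.** That needs almost no uptake in uncounseled women and reach of about 20% to 30% of all women. It is also a crude figure, while the planned model is adjusted.
- **Control-period women inflate it to about 3.6 to 6.1** (h of 5% to 30%). That requires pooling them with no intervention or time term. The displayed example model has both, and nothing says the strategy model drops them.
- **No clinic can have a Happy Client in its first months.** The eligibility text does not imply this. A woman counseled around delivery could qualify quickly, and the pilot counseled 12,068 women or couples. Time since crossover is a possible confounder, not a demonstrated gap.
- **A biased estimate would by itself lead to national roll-out.** No decision rule in the article says so.

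**What to change.** In the Primary analyses paragraph on promotional strategies, do one of the following:

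1. add one-on-one counseling as a term beside CHW counseling, video and Happy Client; or
2. make the main Happy Client contrast counseling with versus without a Happy Client, among counseled women in clinics already in the intervention period.

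In either case, include calendar period and time since the clinic's crossover, define how a joint session is counted, and do not adjust for a promotion count that contains the exposure being estimated.

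This needs no new data collection. The article already plans to record every promotion, and the logbook holds one-on-one counseling. The cost is a smaller analysis set if the restricted contrast is used and probably a less favorable odds ratio. The restricted estimand also excludes any effect of Happy Clients in bringing women to counseling, and the report should say so.
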